## Abstract

**Background:**

The prevalence of substance use disorder (SUD) in people with Mild Intellectual Disabilities or Borderline Intellectual Functioning (MID-BIF) is high. However, an effective personalized treatment for people with MID-BIF and SUD is lacking. This paper describes the study protocol of the effectiveness study of Take it Personal!+, a personalized treatment for people with MID-BIF and SUD.

**Methods:**

The effectiveness of Take it Personal!+ in decreasing substance use will be assessed in a non-concurrent multiple baseline across individuals design comprising ten participants with MID-BIF and SUD. The participants with MID-BIF and SUD will be randomly allocated to one of the five baseline lengths (7–11 days). Substance use, will be assessed during baseline, intervention, and post-treatment phase using a daily diary method.

**Discussion:**

If this study shows that Take it Personal!+ is effective in decreasing substance use, the gap in treatment for people with MID-BIF and SUD will be filled.

**Trial registration:**

The study is registered in the Netherlands Trial Register (Trial NL4935, registered July 2, 2019).

## Introduction

1

The prevalence of Substance Use (SU) in people with Mild Intellectual Disability or Borderline Intellectual Functioning (MID-BIF; 50–85) is alarming [1,2]. People with MID-BIF are more vulnerable to problematic substance use (due to e.g., poor refusal skills and impulse control), and the prevalence of Substance Use Disorder (SUD) in this target group is high, particularly in individuals with comorbid psychiatric disorder, individuals receiving residential or outpatient Intellectual Disabilities (ID) care, and forensic patients [3,4]. Besides, individuals with MID-BIF are at increased risk for developing SUD, due to various risk factors (e.g. impairment in cognitive and adaptive skills, lack of adequate coping skills, peer pressure) [4,5]. SUD has severe adverse health and social consequences for people with MID-BIF [6]. SUD is associated with comorbid mental health problems (e.g., depression and anxiety), behavioral problems (e.g., aggression and criminal activities), social problems (e.g., loneliness, conflicts with families and friends), and financial problems [6,7]. In addition, SUD hinders participation and inclusion in society [1].

Despite the urgent need for SUD interventions for people with MID-BIF, effective interventions that meet the needs of these people and appropriately address the level of SUD severity are lacking. Individuals with MID-BIF do not benefit from regular interventions because these interventions are not adjusted to their needs. People with MID-BIF have deficits in intellectual and adaptive functioning (e.g. in the areas of language, memory, organizing tasks, generalization of learned skills) [8], and interventions need to be adjusted to these needs. Over the past years, a range of interventions have been developed for this vulnerable group [4,5,[9], [10], [11], [12]]. Some of these interventions are educational or preventive or aiming to increase motivation or prevent individuals from start using substances [9,11,12]. However, these interventions fall short in individuals who present with more severe levels of SUD [11,12]. Another point is that the effectiveness of current interventions is mostly unknown due to lack of research [4]. Recently, the focus in mental health care shifted towards more personalized treatment approaches. Personalized treatment seems to be necessary in achieving recovery, and it prevents under- or over-treatment [13]. Personalized interventions are personalized based on characteristics of the client [14]. Current interventions for SUD in individuals with MID-BIF have been designed according to a “one-size-fits-all” mindset, which means that the intervention is not protocolled to target specific characteristics. Take it Personal!+ responds to the need for effective personalized treatment for people with MID-BIF and SUD.

### Take it Personal!+

1.1

Take it Personal!+ is a personalized SUD treatment for people with MID-BIF. The treatment aims to reduce SU. Take it Personal!+ is based on the personality profile (sensation seeking, impulsivity, anxiety-sensitivity, or negative thinking) of the client. Studies have shown that these personality profiles are associated with SU in people with and without MID-BIF [15,16]. Prevention programs based on these personality profiles have shown to be more effective compared to non-personalized prevention [17] and to be effective in decreasing SU in youth with MID-BIF [18]. Preliminary empirical findings suggest that SUD treatment for people with MID-BIF may also benefit from differentiating personality profiles.

Furthermore, Take it Personal!+ is based on Motivational Interviewing (MI) and Cognitive Behavioral Therapy (CBT). MI and CBT are effective methods in decreasing SU in individuals without MID-BIF [19,20] and adapted versions of MI and CBT have shown promising results in increasing motivation and reducing SU in individuals with MID-BIF [9,18,21,22]. In addition, Take it Personal!+ is supported by a mHealth application (TiP!) which supports the transfer-of-treatment to everyday life. Digital support is increasingly being applied in interventions [23,24] and may eliminate problems with generalization and transfer, which are often seen in individuals with MID-BIF.

Take it Personal!+ is adjusted to the needs of individuals with MID-BIF. All communication materials are simplified and supported with pictures, the treatment design with an A and B session ensures repetition and a confidant of the participant is involved during the intervention to stimulate generalization. More information about the adjustments is described in the intervention mapping paper [25].

### The study

1.2

This study aims to evaluate the effectiveness of Take it Personal!+ in decreasing SU in individuals with MID-BIF and SUD. We hypothesize that Take it Personal!+ will decrease SU in these individuals. If confirmed, Take it Personal!+ will fill the current gap in the effective treatment interventions for SUD in people with MID-BIF.

## Methods

2

### Study design

2.1

Data will be collected within a non-concurrent multiple baseline across individuals design [26]. We will examine the effectiveness of Take it Personal!+ in ten participants with MID-BIF and SUD receiving care from healthcare organizations for people with MID-BIF and behavioral problems in the Netherlands. Participants will be randomly allocated to one of the five baseline lengths varying from 7 to 11 days. The onset of the treatment will be randomized, which will maximize internal validity [27]. The design consist of four phases: baseline phase (7–11 days), intervention phase (11 weeks), post-treatment (1 month), and a follow-up phase (3 months after the intervention). The study is conducted between spring 2019 and summer 2020. It is registered in the Netherlands Trial Register (Trial NL4935, registered July 2nd, 2019), and approved by the Faculty Ethics Committee of the Radboud University (ECSW-2019-033).

### Recruitment

2.2

Clients with MID-BIF and SUD will be recruited from different healthcare organizations for people with MID-BIF and behavioral problems to examine the effectiveness of Take it Personal!+ in ten participants. Professionals can invite clients to participate in the study, or clients can ask professionals for a treatment for their SU problem. After the invitation, clients will be informed about the research and given one week to reflect on and sign the informed consent form. Permission of parents or legal representatives will be asked, if necessary. During the intake procedure, the Take it Personal!+ therapist and a physician (e.g., intellectual disability physician, psychiatrist, general practitioner, addiction physician) will assess whether the client meets the following inclusion criteria: 1) diagnosed with a MID-BIF with an IQ between 60 and 85 as assessed by a standardized intelligence test, and deficits in adaptive skills, according to the 5th edition of the Diagnostic and Statistical Manual of Mental Disorders (DSM-5) [8], 2) diagnosed with a SUD with cannabis, alcohol, XTC, cocaine, or speed use according to the DSM-5 [8], 3) substance use at least three days a week, and 4) proficient in Dutch language. Clients will not be eligible if they meet one of the following exclusion criteria: 1) risk of severe withdrawal symptoms, 2) severe psychiatric comorbidity, such as suicidality, psychosis, or major depressive disorder, 3) severe somatic problems, and 4) psychosocial problems that interfere with treatment (e.g. homelessness). Clients that meet the exclusion criteria will be referred to another treatment or treatment centre (e.g., a client with a high risk of withdrawal symptoms will be referred to addiction care).

### Treatment

2.3

The aim of Take it Personal!+ is to decrease SU. The treatment is personalized (i.e., adapted to the participant's personality profile related to SUD), based on MI and CBT and supported by an mHealth application TiP! Take it Personal!+ is based on a CBT-MI protocol for SUD in youths [28] and a CBT-MI protocol for SUD in individuals with MID-BIF [29]. In Take it Personal!+ these protocols are personalized and further developed in collaboration with professionals working in the field of addiction and intellectual disability care.

Take it Personal!+ is designed to last for 11 weeks; however, the therapist can adjust the duration based on the needs of the participant (e.g. if a participant needs more repetition). Take it Personal!+ offers two sessions (Session A and B) of 45 min per week. Session A is an individual session with the participant and in session B the participant brings along a confidant from his/her social network or professional care. Therapists with experience in treating individuals with intellectual disabilities and SUD will carry out the treatment which is based on the therapist manual. All therapists are CBT and MI-certified and experienced in ID treatment.

At intake, the Substance Use Risk Profile Scale (SURPS) [30] will be completed to allocate the participant to one of the four personality profiles. The Take it Personal!+ manual is adapted to the personality profiles and consist of the following key components: 1) motivation to change SU, 2) psycho-education regarding the personality profile, 3) setting goals and making a plan to change SU, 4) identification of personality profile and associated signals of problematic behavior, 5) functional analysis of SU, 6) increasing self-control, 7) behavioral and cognitive coping skills training, and 8) relapse prevention.

The treatment is supported by the mHealth application TiP! The application consists of the following components closely related to the key components of the treatment sessions: 1) exercises (e.g. disadvantages of SU and advantages of changing SU), 2) week goals and how to achieve them, 3) future wishes and how to achieve them, 4) a help! button (i.e. personalized feedback on risk situations, craving, and relapse and the possibility to text or call someone from his/her address book), 5) information about self-control skills, refusal skills, and positive and negative thoughts, and 6) a relapse prevention plan. In addition, gamification by using a personalized avatar and rewards in terms of accessories for the avatar and points for personal rewards makes TiP! appealing for users. For more information about the key components of the treatment and mHealth application see the intervention mapping paper [25]. During the treatment, collaboration with addiction care is important, therapists stay in close contact with different professionals who working in addiction care and are available for consultation.

### Outcomes

2.4

The primary outcome of this study is frequency and quantity of SU. SU will be assessed with daily diary measures during the baseline phase (7–11 days), intervention phase (11 weeks), and post-treatment (1 month). The daily diary method will be applied using a mobile application for cellular phones (Ethica) [31]. Every morning or evening, participants will receive a push notification to complete a short questionnaire within a determined time frame (i.e., varying from 240 min to 780 min). The time of the push notification and the time frame will be decided in consultation with the participant. The questionnaire consists of fifteen questions and is based on previous studies [32,33]. One item will assess the frequency of SU, ‘Did you use *the primary substance* today?’ measured by (1) ‘yes’ and (2) ‘no’ responses. If the participant answers positively, he or she will be asked the second open-ended question, to assess the quantity of SU, ‘How many times?‘. To monitor the frequency of other daily SU, participants will be asked the question, ‘Did you use another substance today?‘, measured by personalized response categories (e.g., (1) ‘no’, (2) ‘yes, alcohol’, (3) ‘yes, XTC’, (4) ‘yes, cocaine’, (5) ‘yes, something else’).

A briefing by the researcher on the daily diary method will take place the day before the start of the baseline phase. In this briefing, attention will be paid to the daily diary procedure, the privacy statement, understanding and personalization of the items, and the time of the daily push notification will be determined. On the second day of the baseline phase, the researcher will visit the participants to check whether the participants have any questions or problems with using the application. If needed, the researcher will plan a second visit later that week [34]. Moreover, during the entire study the researcher will contact the participants if they did not fill in a number of questionnaires. Part of the questions will also be discussed during treatment sessions, where the therapist will evaluate the procedure during the intervention phase.

Additional information on SU will be collected using standardized questionnaires. At baseline, post-treatment, and follow-up, we will use the Substance Use and Misuse in Intellectual Disability - Questionnaire (SumID-Q) [35] to assess the frequency, quantity and severity of SU by the Alcohol Use Disorder Identification Test (AUDIT) [36] and the Drug Use Disorder Identification Test (DUDIT) [37].

To monitor treatment fidelity, therapists will fill out an evaluation form after each session. The form will assess 1) adherence to the manual, 2) dosage, and 3) program differentiation [38].

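### The diary items ask about use *today*, but the prompt may come in the morning or early evening, so use later that day is asked about in no diary

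*Protocol article*

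**What the plan says.** Section 2.4 (Outcomes) of the protocol article names the endpoint: "The primary outcome of this study is frequency and quantity of SU". It is taken from a once-daily app diary through baseline, intervention and post-treatment.

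- Prompt: "Every morning or evening, participants will receive a push notification to complete a short questionnaire within a determined time frame".
- Window: "varying from 240 min to 780 min", that is 4 to 13 hours.
- Who sets them: "The time of the push notification and the time frame will be decided in consultation with the participant".
- Frequency item: "Did you use *the primary substance* today".
- Count item: "If the participant answers positively, he or she will be asked the second open-ended question, to assess the quantity of SU". It therefore inherits the frequency item's reference period.
- Other substances: "Did you use another substance today".

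The same section describes a briefing on the day before baseline that covers "understanding and personalization of the items, and the time of the daily push notification will be determined". A researcher visit follows on the second baseline day. No section gives a different recall period for morning prompts, and no printed item asks about yesterday or about the time since the last diary.

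Section 2.5 (Statistical analyses) analyses the diary series visually and by time series methods, with Kalman-based imputation of missing values.

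**The concern.** A morning prompt and a question about *today* do not fit together. At the moment of answering, most of the day has not happened yet. The next diary asks about its own *today*, so the rest of the earlier day is never covered. An early-evening answer has the same gap on a smaller scale. If a long window runs past midnight, *today* changes date while the diary is still open, and it is unclear which day an answer describes.

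Both parts of the primary outcome are affected. The gap itself acts in one direction, towards too little recorded use. That matters in a design with baselines of only 7 to 11 days, where each person's fall is judged against a short series. It also cannot be put right in the analysis. A completed diary with a false *no* is an observed value, so imputation leaves it alone. The SumID-Q, given at baseline, post-treatment and follow-up (section 2.4), is a useful second measure but cannot rebuild a daily series.

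**Working it through.** The article gives no figure on this point to reproduce. The inputs from it are the morning-or-evening prompt, the 240 and 780 min windows, the *today* wording (all 2.4), the 7-day minimum baseline (2.1) and the entry criterion of use on at least three days a week (2.2). Clock times, use-days per week in steps 3 and 5, and the missed share *s* are assumptions.

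**1. Part of the day not covered.** If *today* runs from 00:00 to completion at hour *h*, the uncovered time is 24 − *h*.

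| Completion | Uncovered | Share of day |
|---|---|---|
| 08:00 | 16 h | 67% |
| 12:00 | 12 h | 50% |
| 18:00 | 6 h | 25% |
| 20:00 | 4 h | 17% |
| 22:00 | 2 h | 8% |
| 24:00 | 0 h | 0% |

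**2. Where the window ends.** Closing time = prompt + window.
- 08:00 + 4 h = 12:00; 08:00 + 13 h = 21:00.
- 20:00 + 4 h = 24:00; 20:00 + 13 h = 09:00 the next day.

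With an 08:00 prompt and the longest window, one participant may answer anywhere from 08:00 to 21:00, so the uncovered time varies from 16 h to 3 h with the prompt unchanged. With a 20:00 prompt and the longest window, *today* changes date before the diary closes. The article does not say which windows go with which prompts.

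**3. Effect on recorded use-days.** Let *s* be the share of use-days on which all use comes after completion. Recorded use-days = true use-days × (1 − *s*). For 5 true days a week:
- *s* = 0.10: 4.5
- *s* = 0.25: 3.75
- *s* = 0.50: 2.5
- *s* = 0.80: 1.0

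**4. Effect on a short baseline.** A participant at the entry minimum has 3 use-days in a 7-day baseline. With *s* = 0.50, 3 × 0.5 = 1.5 are recorded.

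**5. Effect on the phase comparison.** Take a true fall from 6 to 3 days a week, which is 3 days or 50%.

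| *s* before | *s* after | Recorded before → after | Absolute fall | Relative fall |
|---|---|---|---|---|
| 0 | 0 | 6 → 3 | 3 | 50% |
| 0.25 | 0.25 | 4.5 → 2.25 | 2.25 | 50% |
| 0.50 | 0.50 | 3 → 1.5 | 1.5 | 50% |
| 0.25 | 0.50 | 4.5 → 1.5 | 3 | 67% |
| 0.50 | 0.25 | 3 → 2.25 | 0.75 | 25% |

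A constant missed share shrinks the absolute fall and keeps the relative one. A changing share can inflate or hide the effect. A change is plausible, because the diary answers are discussed in treatment sessions (2.4, 3.1), which take place only once treatment has started.

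**The case against.** The strongest reply is that this is a condensed article. Only three of fifteen questions are printed, and the English may be a translation of Dutch items. The briefing covers understanding and personalization of the items, and a visit follows on day 2, so a sensible recall period may be explained there. That stands as a limit on how sure one can be about what happens in practice. It does not remove the mismatch: the item wording is printed, it is the same for morning and evening prompts, and nothing says that the briefing changes the period.

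A reader might infer that the primary outcome is established to be under-recorded, or that every use after completion is lost. The article does not support either. It does not show how participants will read *today* in the morning. Use after midnight can fall into the next date's diary, and late-evening completion loses little.

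A reader might also infer that any change in answering time will show up as a treatment effect. It can, but only if it changes the share of use captured, and it can hide an effect as readily as mimic one. Phases are compared within persons, so a stable loss leaves the relative change intact. Differences in recall interval between participants still matter for the between-person comparison in 2.5. The notification time is already set at the briefing, and nothing says that it changes by phase. What can move is the completion time within a window of up to 13 hours.

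**Conclusion.** The point holds in this form. As printed, the recall period does not match a morning or early-evening prompt, and use between completion and the end of that day is asked about in no diary. Taken literally, this lowers recorded frequency and quantity by an amount that depends on prompt and completion time. On assumed clock times, the uncovered part of the day runs from 67% (08:00) to 8% (22:00).

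The number of use-days lost cannot be derived, because the article gives no time-of-day pattern of use. The values of *s* above are illustrations, and the largest has no support in the text. The absolute phase change shrinks. The relative change is biased, in either direction, only if completion time or time of use shifts between phases. The defect deserves correction because it sits in the primary outcome, cannot be repaired by analysis and is cheap to remove beforehand.

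**What to change.** Give the frequency, count and other-substance items one fixed reference day that leaves no gap and does not depend on the previous diary having been completed. An interval that starts at the last completed diary would stretch after a missed day, so it is not suitable. Examples:

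- Morning prompts: yesterday, from getting up until going to sleep.
- Evening prompts: an equivalent fixed interval that includes use after the previous evening's diary, such as the 24 hours up to the agreed prompt time.

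Date each answer by its reference day, including answers given after midnight. Store the completion time. Keep each participant's agreed slot constant across phases. Report completion times by phase, so that a shift can be seen.

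The cost is rewording the items and the briefing. Recall becomes slightly longer in a group with memory deficits (Introduction), so the wording should be checked with participants. A change of wording in mid-series alters the instrument and could coincide with a phase change. Participants already enrolled should therefore keep one wording throughout their series, or be flagged in the data. If the app already uses another recall period, no item needs to change, and the text of 2.4 should be corrected to state it.

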### Statistical analyses

2.5

To determine whether Take it Personal!+ leads to a decrease in SU, data on SU gathered from the daily diary measures will be analyzed visually and by using time series analysis. Both within-person processes and between-person differences will be studied. Missing data will be imputed using Kalman filtering equations [39] with the R package imputeTS [40]. At least a medium effect size is expected (cf [18]). The results will be reported following the Single-Case Reporting guideline in Behavioral Interventions (SCRIBE) to make the study transparent, to facilitate replication, and to structure the paper.

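### The primary outcome is named as substance use in general, but its frequency and quantity items cover only the primary substance, so a switch to another substance could be read as a decrease

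*Protocol article*

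**What the plan says.** Section 1.2 sets the question for SU as a whole: "This study aims to evaluate the effectiveness of Take it Personal!+ in decreasing SU in individuals with MID-BIF and SUD". Section 2.4 names the endpoint equally broadly: "The primary outcome of this study is frequency and quantity of SU".

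The same section then assigns diary items to that endpoint:

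- **Frequency.** "One item will assess the frequency of SU", and its wording is "Did you use *the primary substance* today", answered yes or no.
- **Quantity.** "If the participant answers positively, he or she will be asked the second open-ended question, to assess the quantity of SU". The question is how many times, and it is reached only after a yes on the primary substance.
- **Other substances.** "To monitor the frequency of other daily SU, participants will be asked the question" whether another substance was used that day, with personalized categories. No quantity question follows in the text.

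Section 2.5 states that "data on SU gathered from the daily diary measures will be analyzed visually and by using time series analysis". It does not say which diary items form the analysed series, or how they are combined. Section 2.4 also provides for the SumID-Q with AUDIT and DUDIT at baseline, post-treatment and follow-up, introduced as follows: "Additional information on SU will be collected using standardized questionnaires".

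**The concern.** The question is about SU, but the items tied to the endpoint record one substance per participant. The two agree only if use of other substances stays constant. If a participant cuts down on the primary substance and takes up another on the same days, a series built from the assigned items falls although the number of days with any use does not.

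That error runs in favour of the treatment. It also carries weight in this design. There are ten participants, and section 3.1 treats agreement of the effect across replications as evidence of generalizability. One or two participants who switch substance could be counted as successful replications.

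**Working it through.** The article gives no figure to reproduce on this point, so the check sets the text side by side and then illustrates the size.

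**1. Outcome against items**

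| Element | Scope in the article |
|---|---|
| Aim and hypothesis (1.2), treatment aim (2.3), analysis question (2.5) | SU in general |
| Primary outcome as named (2.4) | SU in general |
| Item assigned to frequency (2.4) | Primary substance |
| Item assigned to quantity (2.4) | Primary substance, after a yes |
| Other-substance item (2.4) | Frequency only, for monitoring |
| Data analysed (2.5) | SU data from the diary, items not specified |

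The first two rows and the next two do not match. The last row does not settle which applies.

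**2. Effect of substitution on frequency**

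Let *p* be the proportion of days with the primary substance and *o* the proportion with another substance only. Then

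any-use days = *p* + *o*, and change in any-use days = change in *p* + change in *o*.

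The rates below are assumed for illustration; the documents give none. Start from *p* = 0.60 and *o* = 0.10, so any use = 0.70. Let *p* fall to 0.30.

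| Share of the fall replaced | *o* after | Any use after | Fall in primary-substance days | Fall in any-use days |
|---|---|---|---|---|
| None | 0.10 | 0.30 + 0.10 = 0.40 | 30 points | 30 points |
| Half | 0.25 | 0.30 + 0.25 = 0.55 | 30 points | 15 points |
| All | 0.40 | 0.30 + 0.40 = 0.70 | 30 points | 0 points |

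**3. Full substitution in one participant**

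Section 2.2 requires use on at least three days a week and does not tie this to a primary substance. Assume a participant uses only the primary substance on *d* of 7 days at baseline, then moves wholly to another substance on the same number of days.

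| *d* | Primary-substance item | Any-use indicator |
|---|---|---|
| 3 | 3/7 = 42.9% to 0% | 42.9%, unchanged |
| 5 | 5/7 = 71.4% to 0% | 71.4%, unchanged |
| 7 | 7/7 = 100% to 0% | 100%, unchanged |

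**4. What the collected data can support**

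Any-use frequency can be derived for each day, because both yes/no facts come from the same diary. An all-substance quantity cannot, because no quantity question for other substances is described.

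**The case against.** Four arguments stand on the other side.

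- **Exclusion is not stated.** The other-substance item is itself a daily diary measure of SU, so the sentence in section 2.5 can be read to include it. A reader might infer from the monitoring wording that other-substance data enter no outcome, and that a switch would certainly be reported as a decrease. The article says neither. This part of the objection stands and limits the point to what could happen under one natural reading.
- **The treatment is not aimed at one substance.** A reader might infer that it targets only the primary substance and so invites substitution. Section 2.3 states the treatment aim as decreasing SU, and the components listed there are not tied to a primary substance. That inference has no support, and the point does not need it.
- **Substitution is measured.** The daily item would show a switch on visual inspection, and the AUDIT and DUDIT cover alcohol and drugs. This is true of the data collected. But the questionnaires are given at three time points as additional information and cannot correct a daily series, and nothing commits the conclusion to the other-substance item.
- **How items are combined belongs in an analysis plan, and following the treated substance is defensible.** Both are fair. A fuller document may define a combined variable. An any-use indicator has its own weakness: a day of minor use of another substance counts the same as a day of the primary one, which could hide real improvement. This argues against insisting on any use as the primary outcome. It does not remove the mismatch, because the article itself assigns the items to the endpoint, and an analysis plan cannot recover quantities that were not asked.

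**Conclusion.** The point holds in a limited form. The endpoint and hypothesis are stated for SU in general, the items assigned to frequency and quantity cover the primary substance, and the article does not fix how other-substance use bears on the conclusion. If the primary series is built from the items as assigned, substitution could be read as a decrease in SU.

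The size cannot be estimated from the documents. In the illustration, the fall in any-use days ranges from the full 30 points with no substitution to zero with complete substitution. The list of eligible substances in section 2.2 does not show that individual participants use several, so the calculation shows a direction and a limit, not a likelihood. The conclusion also assumes that no document outside the article already defines a combined variable. It is a cheap improvement worth making, not evidence that the planned result would be wrong.

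**What to change.** 1. State whether SU in the primary outcome means primary-substance or any-substance use. Primary-substance frequency and quantity may stay as they are.
2. Derive a daily any-substance indicator (yes to either item) and analyse it for each participant by the same visual and time series methods.
3. Conclude that SU decreased only where any-substance days also fall. Otherwise name the primary substance in the conclusion.
4. State that the quantity result applies to the primary substance only.

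**Cost.** No new data collection and no change to the diary: one more derived series per participant. The claim may become smaller or narrower. The any-use indicator gives minor use of another substance the same weight as use of the primary one, which is a reason to report the two series side by side.
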